### Randomisation

Once an ascitic tap has excluded peritonitis (defined as ascitic white cell count > 500 cells/mm^3^ or a neutrophil count > 250 cells/mm^3^ or a positive ascitic-fluid culture result)[19] participants will be registered by the local teams on an electronic data capture platform (Ennov:MACRO™) [32] and then randomised to receive either LTAD or standard of care (LVP) in a 1:1 ratio using Sealed Envelope™ [33]. The computer-generated software will confirm the patient’s treatment group allocation. The allocation will be minimised (i.e. dynamically generated) on sex and Child–Pugh Score (CPS) with an 80% probability of assigning participants to the group that balances these factors out. This will ensure comparability of the two groups. Only the trial manager, Chief Investigator (CI), and central research team will be aware of the exact sequence of the most recent allocations. Blinding researchers or participants is not feasible due to the nature of the intervention. However, the senior trial statistician will remain blinded until final data analysis, with adverse events (AEs) coded to prevent unintentional unblinding.

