#### Community LTAD management

Participants will receive an initial supply of compatible drainage kits and specific trial paperwork, such as drainage diaries for community nurses to record the volume and frequency of drainage. If keen and willing, caregivers will be given an opportunity to perform the drainage themselves, supported by the community nursing teams. However, the diaries should only be completed by the community nurses, who will perform risk assessments during their home visits and raise any concerns regarding the LTAD with the research team.

Frequency and volume of drainage through the LTAD in the community will be guided by the patient’s symptoms but generally should not exceed one to two litres at each visit and no more than two to three times a week (i.e. five litres per week). This was initially based on volumes used in malignant ascites [22], but was also sufficient for ascites management in 90% of patients in the earlier feasibility study [29]. In the minority needing drainage of larger volumes, an LVP via the LTAD can be arranged in hospital, including HAS administration. Subsequent drainage volumes can then be increased in the community on a case-by-case basis.

LTAD removal should only be considered at the participant’s request, or in the event of certain complications, for example intractable infection. Continued trial participation will be encouraged, despite LTAD removal. Re-insertion of LTADs can be organised if necessary, on a case-by-case basis. Appendix 3 summarises potential complications associated with the LTAD and a recommended management protocol for each.

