### Sample size calculation

The minimal clinically important difference (MCID) is the mean change in HRQoL scores for patients reporting a minimal yet perceptible change in health between the baseline and follow-up assessments [47]. In the ongoing LiverPal Study (one of the largest palliative trial in the USA [48], an MCID of 9 points on the FACT-Hep questionnaire was used [49]; and in a study assessing LTADs in cirrhosis,[50] an MCID of 10 points was chosen (SF-36 questionnaire[42]). While these studies show the use of MCID to inform sample size in palliative trials, neither of the tools selected are validated in ACLD. As we will be using the SFLDQoL [37], a sensitive and validated ACLD questionnaire, and to ensure a robust sample size, we have selected a MCID of 8 points.

In the earlier REDUCe trial [29], the pooled baseline mean across SFLDQoL domains (excluding sexual function) was 56.4 (SD = 26.1). With 93 participants in each group for the analysis, we will have 90% power for 5% significance to detect an adjusted difference in mean SFLDQoL scores of 8 points between the LTAD and LVP groups at the end of 3 months (effect size 0.31). This effect size falls within Cohen’s recommended cut offs for small (0.20) to moderate (0.50) effect size [51]. We assume a correlation between baseline and the 3 follow-up measurements of 0.48 which is the lower bound of the 95% confidence interval for the correlation from the feasibility data (point estimate 0.77) [29]. With an expected 40% attrition [29], we will recruit 310 participants in total for the trial. The sample size was calculated using Stata (version 17.0).

Following on from lessons learnt during the earlier feasibility study [29], to improve study retention, the protocol allows for proxy-scores to be collected on behalf of patients who may be too unwell to complete the questionnaires themselves. Secondly, appointment of consultees who can be approached in case of loss of capacity during the trial follow-up period will allow patients to be retained even in case of disease progression. Finally, to prevent recruitment late in their disease trajectory, we are providing communication skills training for researchers to facilitate difficult palliative care discussions.

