**Fig. 4 Fig4:**
[figure not shown]
CONSORT diagram. Abbreviations: n number, LTAD long-term abdominal drain, LVP large volume paracentesis

For the primary outcome, the analysis will follow intention-to-treat principles and will be conducted using a linear mixed effects model. All patients randomised through Sealed Envelope will be included in the group to which they were allocated regardless of the outcome or clinical trajectory.

This model will include fixed effects: time point, sex, Child Pugh score, randomisation group, and an interaction between randomisation group and time point, while adjusting for baseline SFLDQoL scores. A random effect for participant will be included to handle the correlation between repeated measurements across the study period. The model parameters will be estimated using restricted maximum likelihood, and treatment differences between groups at each follow-up will be reported along with 95% confidence intervals and p-values. Secondary outcomes will similarly be analysed using mixed effects regression models suited to the type of outcome.

Subgroup analyses will aim to stratify data based on patient and site-level characteristics. Patient-level factors will include liver prognostic scores baseline ascitic fluid protein level, socioeconomic status, and the presence of informal caregivers. Site-level data will include prior experience with LTADs, availability of dedicated LVP units, cirrhosis nurses, Palliative care MDTs for ACLD, and Improving Quality in Liver Services (IQILS) programme accreditation. Subgroup analyses will allow for the identification of potential effect modifiers or predictors of outcomes and changes in HRQoL.

Only in the case of significant protocol deviations, agreed with the CI, will participants be excluded from the final analysis. In accordance with MORECare guidance for palliative trials, attrition due to mortality, illness, and withdrawal will be detailed for each group [53]. Missing quantitative data will be assumed to be missing not at random (MNAR) unless evidence suggests otherwise. Imputation models will be utilised followed by sensitivity analyses using plausible adjustments to explore the potential impact of missing data and MNAR assumptions on treatment outcomes (multiple imputation with delta adjustment).

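### The plan promises to analyse every randomised patient as allocated, yet lets patients be excluded from the final analysis for protocol deviations agreed with an allocation-aware chief investigator

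*Protocol article*

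**What the plan says.** Three statements in the protocol article's Statistical analysis section (under Data analysis) bear on who is analysed.

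- The principle: "For the primary outcome, the analysis will follow intention-to-treat principles and will be conducted using a linear mixed effects model".
- The population: "All patients randomised through Sealed Envelope will be included in the group to which they were allocated regardless of the outcome or clinical trajectory".
- The exception, three paragraphs later: "Only in the case of significant protocol deviations, agreed with the CI, will participants be excluded from the final analysis".

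The article does not define a significant deviation, and it does not say that exclusions are decided without sight of allocation or outcome.

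The Randomisation section describes who knows what. On allocation: "Only the trial manager, Chief Investigator (CI), and central research team will be aware of the exact sequence of the most recent allocations". On blinding generally: "Blinding researchers or participants is not feasible due to the nature of the intervention". One role is kept blind: "However, the senior trial statistician will remain blinded until final data analysis". The exclusion rule gives that role no part.

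**The concern.** Intention to treat protects the comparison because membership of each arm is fixed by randomisation and by nothing that happens later. A rule that removes patients for events after randomisation gives up that protection if those events, or the judgement that they are significant, relate to both arm and prognosis. Here the judgement needs the agreement of someone who knows the allocations, and its key term is left open.

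At stake is the membership of the primary analysis in a trial that its authors present as definitive. If the exclusion sentence is followed, the result is no longer the all-randomised comparison that the plan promises. If the inclusion sentence is followed, the exclusion sentence has no application. An analysis plan written later could follow one only by breaching the other, so this is a conflict in what the article states and not a detail left for elsewhere.

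**Working it through.** **1. Can both rules hold?** Take a randomised patient with outcome data and a deviation judged significant. The population statement keeps that patient in the allocated arm; the exception takes the patient out. Two readings might reconcile them.

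- The final analysis could mean some set other than the primary analysis. The article names no other set. The Randomisation section also uses a near-identical term for the moment when the senior statistician is unblinded, which points to the main analysis.
- The exception could be a deliberate carve-out from intention to treat. The primary population is then no longer all randomised patients, which is what the population statement says it is.

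Neither reading leaves both sentences true as written.

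**2. Who decides, and with what knowledge?** The chief investigator must agree, and the Randomisation section lists that role among those aware of allocations. So the decision can be allocation-aware. The article does not state whether outcome scores are also visible at that point.

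**3. The plan's own sample size.** Inputs from the Sample size calculation section: effect size 0.31 (8/26.1 = 0.3065 before rounding), correlation 0.48, three follow-ups, 90% power, 5% significance (two-sided assumed), 40% attrition.

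- Variance factor for one baseline and three follow-ups: (1 + 2 × 0.48)/3 − 0.48² = 0.4229.
- n per arm = 2 × ((1.960 + 1.282)/0.31)² × 0.4229 = 92.5, so 93. With the unrounded effect size it is 94.6, so 95.
- Total: 186/(1 − 0.40) = 310.

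The stated 93 and 310 reproduce. With 93 per arm and the unrounded effect size, power is 89.5%. The implied standard error of the difference is √(2 × 26.1² × 0.4229/93) ≈ 2.5 points.

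**4. What exclusions could do to the estimate.** Suppose a fraction f of an arm is removed and those patients score k points below the patients kept. The full-arm mean is (1 − f) × kept + f × (kept − k) = kept − f × k, so exclusion raises that arm's mean by f × k. The between-arm difference shifts by f × k in one arm minus f × k in the other. The article gives no deviation rate and no score gap, so these figures for exclusions in one arm only are assumptions:

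- f = 5%, k = 10: 0.5 points (6% of the 8-point target; 0.2 standard errors).
- f = 5%, k = 20: 1.0 point (12.5%; 0.4 standard errors).
- f = 10%, k = 10: 1.0 point (12.5%; 0.4 standard errors).
- f = 10%, k = 20: 2.0 points (25%; 0.8 standard errors).

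If exclusions were equally frequent and equally prognostic in both arms, the shift would be zero. If they fell in the other arm, its sign would reverse. These are shifts in unadjusted means. The planned model adjusts for baseline score, so any part of the gap already present at baseline would be partly removed.

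**5. What exclusions could do to power.** Losing a further 5%, 10% or 20% of analysed patients in both arms takes power from 89.5% to 88.0%, 86.2% or 82.0%. These rates are also assumed. Selective exclusion matters mainly for bias; the precision cost is modest.

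**The case against.** The strongest defence is that the authors meant something narrow. The exception is worded restrictively, intention to treat is stated plainly, and the population statement keeps in patients who do badly. Agreement with the chief investigator does not make that role the only decider. Attrition will be detailed by group and patient flow shown in a CONSORT diagram, so exclusions might well be visible. All of this is fair and suggests a drafting slip more than an intention to select patients. It does not remove the conflict: the inclusion of all randomised patients is unqualified, and the exclusion is not confined to a secondary set.

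A reader might also infer that exclusions would fall mainly on the LTAD arm, would remove that arm's failures and so favour LTAD, and would be decided once outcomes were known. The article does not support this.

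- The Community LTAD management section allows drain removal in stated circumstances and adds: "Continued trial participation will be encouraged, despite LTAD removal". Its drainage volumes are general guidance that can be varied case by case.
- The LTAD insertion section gives a rescreening route when the insertion window is missed.
- Several requirements bind both arms, including exclusion of peritonitis, antibiotic prophylaxis, fortnightly visits and a 10-day window to the baseline visit.
- No timing, rate or arm split of exclusions is given. Liver-specific quality-of-life data are checked by a separate team and held on a separate database, and nothing says the chief investigator sees those scores when agreeing an exclusion.

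These objections stand against any claim about direction, timing or expected size. They leave the contradiction and the allocation-aware discretion untouched.

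**Conclusion.** The exclusion rule is wrong as written. It contradicts the all-randomised population stated in the same section, and it allows exclusions after randomisation with the agreement of someone who knows the allocations. That could bias the primary comparison. Neither direction nor size can be derived from the article; the 0.5 to 2.0 points shown against a target of 8 rest on assumed exclusion rates and score gaps, one-sided exclusion and no baseline adjustment. The conclusion itself rests only on the text: the two sentences conflict, no separate analysis set is named, and the chief investigator is not blind to allocation. The sample size is not in question.

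**What to change.** Remove the exclusion sentence as it applies to the primary and other intention-to-treat analyses, so that all randomised patients are kept as allocated.

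If an analysis by adherence is wanted, make it a labelled supplementary analysis. Fix its list of qualifying deviations before the final analysis, and have the criteria applied without sight of outcome data. Mask allocation too where the type of deviation allows. Full masking will not always be possible, because a drain-related deviation reveals the arm.

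The cost is one sentence and one optional supplementary analysis. The 93 per arm and 310 in total stay as they are. Last patient last visit is planned for September 2026, so the change should be made before the final analysis.

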### Health economic analysis

The health economic analysis will adopt a health and social care perspective. Whole system costs for LTAD and LVP will be compared to assess if community drainage is resource saving compared to hospital drainage. Items of service use will be converted to costs (British pounds 2023) using nationally validated unit costs [54], and NHS reference costs [55]. Time spent by informal caregivers will be valued using replacement cost methods and applying the tariff for community support workers [56]. Costs for each main category of resource use (primary, community, hospital, social, voluntary, informal) will be reported as mean, standard deviation and median (range, IQR). Since patients will be in the study for different durations, the data will be standardised for fortnightly analysis, if necessary, for meaningful comparisons.

A within trial cost-effectiveness analysis will be conducted based on three-month follow-up. EQ-5D-5L utilities will be reported at each follow-up time point as mean and standard deviation. QALYs per patient will be calculated using the area under the curve approach. Use of QALYs in palliative care remains controversial, due to problems with conceptualising HRQoL, restrictions in life years gained and valuation of time. However, QALYs are widely used and in the absence of well recognised alternatives, they offer useful data for health policy makers [53, 57].

Differences in costs and QALYs will be estimated using linear mixed effects models, in line with the statistical approach to other outcomes (QALYs adjusted for baseline utility [58] and used to compute cost per QALYs of LTAD vs. LVP. Uncertainty will be characterised using probabilistic unit costs and non-parametric bootstrapping with replacement techniques in estimation processes.

### Qualitative data analysis

Thematic analysis supported by qualitative software (NVivo™) [59] will be used to develop overarching themes from the interviews. Interviews will be analysed separately for the three groups of participants (patients, informal caregivers and HCP) after which themes will be compared across participant groups to explore overlap or discrepancies. Utilising the process of triangulation [60], the findings of the qualitative arm will be used to contextualise the quantitative results as they relate to HRQoL.

### Ancillary and post-trial care

Routine clinical care of participants will not be affected by participation in the trial. At the end of the study, participants will continue routine care with their medical teams. Those randomised to LTAD can opt to retain it, or have it removed. Those on the SOC arm can be offered a LTAD outside the trial setting after study completion on a case-by-case basis. The sponsor will provide indemnity cover for negligent harm if applicable.

### Monitoring and trial committees

#### Site monitoring plan

The trial manager will conduct remote or in-person monitoring at each site, as outlined in a pre-approved Monitoring Plan. Monitoring frequency will depend on recruitment, withdrawals, and adverse events at each site. These visits will review participant enrolment, consent, eligibility and trial arm allocation, and ensure adherence to interventions, harm reporting, and data collection accuracy.

### Trial management group (TMG)

The TMG, consisting of research team members from each site, will be chaired by the CI and meet monthly. These meetings will troubleshoot any site issues including recruitment, review proposed changes to trial documents, and ensure timely trial completion.

### Trial Steering Committee (TSC)

The TSC, comprising independent members (two hepatologists one of whom will be the chair, a statistician, and PPI member), the trial CI, trial manager and trial statistician, will oversee trial conduct and recruitment on behalf of the sponsor and funder. Meeting biannually, the TSC will review study progression, considering safety reports issued by the Data Safety and Monitoring Committee (DSMC).

### Data Safety and Monitoring Committee (DSMC)

The DSMC, an independent committee including a hepatologist (chair), statistician, and palliative care physician, will review study data following its terms of reference. The DSMC will meet approximately every six months and address safety concerns, ethical issues, and adverse events, providing recommendations to the TSC.

### Role of PPI

The PPI group have been involved since the feasibility trial [29] and helped shape the research methodology, outcome measures and assessment tools. PPI members were co-applicants on the grant application, are part of the TMG and will be co-authors on any publication(s).

### Role of the sponsor and funder

The study sponsor and funder had no role in the study design, nor the collection, management, analysis and interpretation of data. They will not be involved in the writing of any reports. The sponsor however will ensure appropriate procedures are in place for reporting progress and safety monitoring and that there is a clear strategy for dissemination of research findings.

### SPIRIT guidelines

The SPIRIT reporting guidelines have been used in this manuscript [61], with the checklist found in Appendix 5 and the SPIRIT figure shown as Table 1.

## Discussion

Running a palliative RCT in ACLD is challenging, with barriers at all stages, including selection of appropriate outcome measures, recruitment, and addressing missing data. This may explain the lack of evidence-based palliative interventions in ACLD [31]. Encouragingly however, national and international guidelines, including NICE, have recently highlighted the need for further research on the use of palliative LTADs in RA [19, 30, 62]. The REDUCe2 study aims to address this knowledge gap and advance the field of palliative care in hepatology.

The trial has several strengths, one of which is its inclusive design to include district general, secondary and tertiary hospitals as well as participants from a range of socioeconomic backgrounds and sites with a high liver disease prevalence. This will enhance the study’s generalisability and validity. Another strength is the close collaboration with our PPI group in the trial design, which ensured selection of appropriate assessment tools and outcome measures, as well as incorporating caregivers’ perspectives. Finally, since this study cuts across healthcare boundaries, it will promote collaboration between hospital and community trusts, aligning with the vision of future healthcare delivery being closer to home [63].

The home research visits, however, are not without their challenges. Although critical for patient follow-up, especially in a palliative trial, they are logistically demanding. This has precluded trial participation for a few sites. However, direct delivery teams from some Clinical Research Networks have had capacity to assist sites with these visits. Additionally, each site is only expected to recruit a small number of patients per year and the study has a short follow-up period. Another contentious issue is that since patients with RA are a heterogeneous group, timely recruitment along their disease trajectory can be challenging. Rapid deterioration can occur, in keeping with the fluctuating nature of ACLD, and interventional procedures in the final days or weeks of patients’ lives may not be appropriate.

The potential impact of the successful completion of the REDUCe2 trial could be substantial. Besides providing high-quality evidence for the palliative management of RA in ACLD, it could also serve as a blueprint for future palliative trials in hepatology.

## Trial status

Current protocol v9.0 28.08.2024. Appendix 6 summarises the protocol amendments to date. The study commenced in May 2022 with a six-month study set up period, active recruitment starting in Nov 2022 and planned to run to Sept 2026 (Last Patient Last Visit), with a final 4 months for data analysis. An 18-month internal pilot was successfully completed in Jan 2024 (see Appendix 7 for STOP–GO criteria).

